### Procedures

The recruitment of participants began in 2018 at Karakter, with a break in 2020 due to COVID-19. The recruitment is ongoing and is expected to be completed by 2024. All adolescents referred to Karakter sent a brief screening questionnaire called the Child Trauma Screening Questionnaire (CTSQ) [21]. This self-report questionnaire asks about traumatic life events, such as domestic violence, sexual abuse, or physical abuse. The research team screens the results from the CTSQ. If multiple traumatic life events are reported and the adolescent shows elevated scores on questions related to post-traumatic stress, the involved healthcare provider is contacted. The healthcare provider is informed about the MARS study and asked to consider participation in the study. The inclusion and exclusion criteria are verified by the medical staff involved with the participants. With the agreement of the healthcare provider and parents/legal guardians, the adolescent is invited to participate in a clinical structured interview (CAPS-CA).

After the CAPS-CA interview, the diagnostic results are discussed with the research team and treatment team of the MARS-study. A conclusion is drawn regarding whether the inclusion criteria for PTSD due to multiple interpersonal traumas are met. An advisory consultation will be scheduled with the participants and parents/guardians if the inclusion criteria are met. During this consultation, the participant is informed about their participation in the treatment study, informed consent is reviewed, and an information sheet about the study is provided. After the advisory consultation, the adolescents and parents/guardians have two weeks to decide whether to participate in the study. If the adolescents and their parents/guardians agree to participate, the randomization procedure is initiated, and a treatment provider is assigned within three weeks. The MARS-study requires written informed consent from both parents and adolescents. In addition, general practitioners are informed through postal letters.

### Interventions

#### Skills training in affective and interpersonal regulation (TRAP; dutch version of STAIR-A)

In Phase I of the phase-based treatment, we use an adapted version of the Skills Training in Affective and Interpersonal Regulation for Adolescents [12]. The purpose of this treatment is to address problems with affect and interpersonal regulation (as they negatively impact daily life) and to effectively utilize trauma-focused treatment. The program consists of twelve sessions, with different topics (e.g., distress tolerance, different kinds of role-plays, labelling and identifying feelings, enhancing adequate coping strategies, training self-soothing skills, etc.). All TRAP sessions have an identical format and structure: psycho-education about the rationale and goals of interventions, skills acquisition, skills application, and practice.

#### EMDR therapy

The protocol for EMDR therapy is an evidence-based trauma treatment aimed at resolving symptoms resulting from disturbing or unprocessed life experiences [22]. Treatment starts with recalling the traumatic memory and selecting the most disturbing part of this memory with associated dysfunctional thoughts and feelings. While concentrating on the traumatic memory, the participant’s working memory is taxed by employing eye movements for approximately 30 s. Repeatedly, the participant is asked to report what comes to mind, which may be cognitive, emotional, somatic, or imagistic experiences. After some sets of eye movements, the participant is asked to report a Subjective Unit of Disturbances (SUD) between 0 and 10, until the disturbance related to the memory reaches an SUD of zero and positive beliefs are rated strong on a VoC (Validity of Cognition, between 1 and 7). A wide array of studies support the working memory account as a mechanism that explains treatment effects. Recalling a traumatic episode depends on limited working memory resources. If a second task, taxing working memory, is executed during the recall of traumatic memory, fewer resources will be available to recall the traumatic episode. By performing both tasks simultaneously, the memory becomes less vivid and emotional and is stored in this new way. Consequently, negative cognitions lose credibility, and positive cognitions become more credible [23].

### Measurements

The study parameters are listed in Table 1. In order to collect data to answer the research questions, it will take the adolescent each time (T1, (T2), T3, T4) about 90–120 min to complete the interview and questionnaires. The total estimated burden for parents/legal guardians to complete the questionnaires will be approximately 120 min. Participants allocated to the TRAP + EMDR condition will undergo a mid-treatment assessment (T2) to investigate the effect of TRAP on both the primary and secondary outcomes.

**Table 1 Tab1:** Study parameters

	Instrument	Informant	Nr. Items	**TRAP + EMDR**					**EMDR only**				
				T0	T1	T2	T3	ES	T0	T1	T2	T3	ES
Screening	CTSQ	Adolescent	24 items	x					x				
*Baseline*													
Demographic variables	Intake Questionnaire	Medical files			x					x			
Dissociative Experiences	A-DES	Adolescent	30 items		x					x			
*Primary outcome*													
PTSD-assessment	CAPS-CA	Adolescent	interview	x	x	x	x		x	x		x	
*Secondary outcome*													
Interpersonal problems	ECR-RC-mother	Adolescent	12 items	x	x	x	x		x	x		x	
Interpersonal problems	ECR-RC-father	Adolescent	12 items	x	x	x	x		x	x		x	
Emotion regulation	DERS	Adolescent		x	x	x	x		x	x		x	
Self Esteem	RSES	Adolescent	10 items	x	x	x	x		x	x		x	
Anxiety and Mood	RCADS	Adolescent	47 items	x	x	x	x		x	x		x	
Posttraumatic cognitions	CPTCI	Adolescent	25 items	x	x	x	x		x	x		x	
Behavior problems	CBCL	Medical files	113 items	x					x				
Behavior problems	Y-OQ-30	Parent	30 items	x			x		x			x	
Parental Stress	OBVL	Parent	34 items	x			x		x			x	
*Other measurements*													
Adherence		Medical files						x					x
Monitoring PTSD	CRIES-13	Adolescent	13 items					x					x
Patient-therapist relationship	SRS/ORS	Adolescent	8 items					x					x

*T0* screening, *T1* baseline, *T2* Mid treatment, *T3* post-treatment, *T4* 6-month follow-up, *ES* each session

### Screening for traumatic experiences

#### The child trauma screening questionnaire

The Child Trauma Screening Questionnaire (CTSQ) [21] is a self-reported measure that contains a 14 items list of traumatic life events and a 10 items list to index post-traumatic stress symptoms of re-experiencing and hyperarousal. Each life event can be answered with yes (scored as 1) or no (scored as 0). Scores > 4 indicate positive screening for trauma symptoms. The CTSQ has been shown to have good convergent validity [21]. Internal consistency was reported, with a Cronbach’s alpha of 0.69.

### Primary outcome

#### The clinician-administered ptsd scale for children and adolescents

The Clinician-Administered PTSD Scale for Children and Adolescents (CAPS-CA) [24] is a structured clinical interview used to establish the diagnostic status of the DSM-IV and DSM-V criteria for PTSD. The interviewer can rate the frequency and intensity of each symptom on a five-point Likert scale. Furthermore, each symptom can be rated as present or absent, as proposed by Weathers, Ruscio, and Keane [25] to score a symptom as being present. The CAPS-CA can be reliably administered by different interviewers. The Dutch CAPS-CA showed as good internal consistency, inter-rater reliability, convergent and divergent validity, and concurrent validity as the original English version [26]. The CAPS-CA will be administered three times (T1, T3, and T4) for adolescents in the EMDR-only group and four times in the TRAP + EMDR group (T1, T2, T3, and T4). Adding the CAPS-CA at T2 in the TRAP + EMDR condition will provide information about the effects and necessity of skills training TRAP as a standalone treatment.

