**Methods:**

Participants are individuals between 12 and 18 years who meet the diagnostic criteria for PTSD due to repeated sexual abuse, physical abuse, or domestic violence during childhood. Participants will be blindly allocated to either the phase-based or immediate trauma-focused treatment condition. In the phase-based treatment condition, participants receive 12 sessions of the Dutch version of Skill Training in Affective and Interpersonal Regulation (STAIR-A), followed by 12 sessions of EMDR therapy. In the immediate trauma-focused condition, the participants receive 12 sessions of EMDR therapy. The two groups are compared for several outcome variables before treatment, mid-treatment (only in the phase-based treatment condition), after 12 trauma-focused treatment sessions (post-treatment), and six months post-treatment (follow-up). The main parameter is the presence and severity of PTSD symptoms (Clinician-Administered PTSD Scale for Children and Adolescents, CAPS-CA). The secondary outcome variables are the severity of complex PTSD symptoms (Interpersonal Problems as measured by the Experiences in Close Relationship-Revised, ECR-RC; Emotion Regulation as measured by the Difficulties in Emotion Regulation Scale, DERS; Self Esteem as measured by the Rosenberg Self Esteem Scale, RSES), changes in anxiety and mood symptoms (Revised Anxiety and Depression Scale; RCADS), changes in posttraumatic cognitions (Child Posttraumatic Cognitions Inventory, CPTCI), changes in general psychopathology symptoms (Child Behavior Checklist, CBCL), and Quality of Life (Youth Outcome Questionnaire, Y-OQ-30). Furthermore, parental stress (Opvoedingsvragenlijst, OBVL) and patient-therapist relationship (Feedback Informed Treatment, FIT) will be measured, whereas PTSD symptoms will be monitored in each session during both treatment conditions (Children’s Revised Impact of Event Scale, CRIES-13).

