## Method

### Study design

This study entails a single-blind, randomized controlled trial with two arms: a phase-based treatment condition (TRAP followed by EMDR) and a trauma-focused treatment condition (EMDR only). In the TRAP-EMDR condition, participants receive 12 sessions of skills training (TRAP; the Dutch adolescents version of the STAIRS protocol), followed by 12 sessions of EMDR therapy. In the other condition, the participants receive 12 EMDR sessions. The two groups will be compared for several outcome variables before treatment, immediately after 12 sessions (post-treatment), and six months post-treatment (follow-up) (see Fig. 1). This study will be coordinated by the Karakter Academic Center for Child and Adolescent Psychiatry in the Netherlands. The study started in 2018, paused for seven months in 2020 due to COVID-19, and continued in September 2020. This study is ongoing and is expected to be completed by 2024.

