## Discussion

The present paper describes the rationale, study design, and methods of the MARS-study: an RCT evaluating the effects of a phase-based treatment model compared to purely trauma-focused therapy in young individuals diagnosed with PTSD and on the possible symptoms of complex PTSD resulting from (repeated) sexual and/or physical abuse during childhood.

This study had several strengths. First, it sought to assess the effectiveness and efficacy of two widely utilized treatment models in a group of patients who are often overlooked in research owing to their complex symptomatology. To the best of our knowledge, an efficacy study of adolescents who have experienced (repeated) sexual and/or physical abuse during childhood is unprecedented. Second, although a phase-based trauma-focused model has recently been studied in adults (15–17), no similar study has been conducted in adolescents. Research on the effectiveness of trauma treatment in adolescents (symptoms of complex) PTSD is limited [20]. To our knowledge, this is the first randomized controlled trial to investigate and compare the effects of regulation skill training with those of a direct trauma-focused treatment approach in this population. Third, adding a follow-up period allows us to track the long-term effects of both treatments, which can provide valuable information about the sustainability of the treatment effects and whether there are any delayed or long-term benefits (sleeper effects) or side effects. Therefore, we can make more reliable and comprehensive conclusions regarding the effectiveness of and differences between interventions. Additionally, by adding a mid-treatment measurement, it is possible to investigate the effects of TRAP and better assess the added value of this phase-based treatment approach.

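### The T2 assessment exists in one arm only, so it cannot show the effect or necessity of TRAP; a randomised comparison at about equal time is available in the same schedule and should be prespecified as supportive

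*Protocol article*

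**What the plan says.** Three places in the protocol article give T2 a causal purpose.

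- The CAPS-CA section under Primary outcome says that adding the interview at T2 "will provide information about the effects and necessity of skills training TRAP as a standalone treatment".
- Measurements says that participants in TRAP + EMDR "will undergo a mid-treatment assessment (T2) to investigate the effect of TRAP on both the primary and secondary outcomes".
- The Discussion counts this as a strength: with the mid-treatment measurement "it is possible to investigate the effects of TRAP and better assess the added value of this phase-based treatment approach".

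The EMDR-only arm has no T2: "The CAPS-CA will be administered three times (T1, T3, and T4) for adolescents in the EMDR-only group". Study design gives TRAP + EMDR 12 TRAP sessions and then 12 EMDR sessions, while "In the other condition, the participants receive 12 EMDR sessions". The abstract places post-treatment (T3) "after 12 trauma-focused treatment sessions (post-treatment"). T3 therefore follows 24 sessions in one arm and 12 in the other.

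Study design compares the groups before treatment, at post-treatment and at six months. Statistical analysis names no analysis of T2. It gives a repeated-measures ANCOVA without listing time points, T1 to T3 delta-scores for the secondary outcomes, and a CRIES-13 mixed model over all time points with a time by condition term.

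**The concern.** An assessment made in one arm, with no concurrent control, yields only a before-after change. Entry requires meeting PTSD criteria on the CAPS-CA (Participants, first inclusion criterion), so the group is selected for being high on the instrument that is then repeated. Part of any fall by T2 would be expected without TRAP. The necessity of TRAP is further out of reach, because it asks whether outcomes after EMDR differ with and without prior TRAP. That is a comparison between arms at the end of treatment.

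Whether a stabilisation phase is needed is the dispute the trial was set up to inform (Background). If an uncontrolled change is offered as evidence on it, readers may give that change a weight the design does not support. Meanwhile, a randomised comparison that can be formed from the same visits is not described for CAPS-CA or the T2 questionnaires.

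**Working it through.** **Inputs.** From Sample size and power: SD 10.4, correlation 0.5 (design factor 0.75), margin 5, assumed true difference -1.82, 38 per arm planned, 27.4 per arm before inflation. From Participants: weekly sessions.

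**The plan's own figure.** n = 7.85 × 10.4² × 2 / (-1.82 - 5)² = 1698.1 / 46.51 = 36.5 per arm. Then 36.5 × 0.75 = 27.4, and 27.4 × 1.4 = 38.4, taken as 38. The article's figures reproduce and nothing below changes them.

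**What the T1 to T2 change can show.** SD of change = 10.4 × √(2 × (1 - 0.5)) = 10.4. With 38 in the arm, SE = 10.4 / √38 = 1.69 and the 95% half-width is 1.96 × 1.69 = 3.31. Suppose TRAP does nothing and the non-specific fall is δ. The probability of a significant fall is Φ(δ/1.69 - 1.96):

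| Non-specific fall δ | Probability of p < 0.05 |
|---|---|
| 3 points | 0.43 |
| 4 points | 0.66 |
| 5 points | 0.84 |

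For δ = 5 the probability runs from 0.71 to 0.97 as the correlation goes from 0.3 to 0.7 (an assumed range). The values of δ are illustrations. The article gives no estimate of change without treatment.

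**Regression to the mean, illustration only.** Expected fall = (1 - correlation) × (enrolled mean - referred-population mean). The article gives no referred-population mean. An assumed gap of 5 to 10 points with correlation 0.5 gives 2.5 to 5 points. The article's 0.5 is itself an assumption made for covariate adjustment, not a retest correlation among referrals.

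**The randomised contrast in the schedule.** Each of these visits follows 12 sessions:

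| | TRAP + EMDR | EMDR-only |
|---|---|---|
| After 12 sessions | T2 (12 TRAP) | T3 (12 EMDR) |
| After 24 sessions | T3 (12 TRAP, 12 EMDR) | none |

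With weekly sessions, the two visits in the first row fall at about the same time since randomisation. Adjusted for T1, the SD is 10.4 × √0.75 = 9.01, and SE = 9.01 × √(2/n):

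| n per arm | SE | 95% half-width (1.96 × SE) | Difference detectable with 80% power (2.80 × SE) |
|---|---|---|---|
| 38 | 2.07 | 4.05 | 5.8 |
| 27 | 2.45 | 4.80 | 6.9 |

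A t quantile raises the half-widths to about 4.1 and 4.9. With 38 per arm, correlations of 0.3 to 0.7 give 4.5 to 3.3.

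**The case against.** The strongest reply is that the article states a purpose for T2, not an analysis. A reader might infer that any T1 to T2 fall will be reported as TRAP's effect. Statistical analysis does not say so, and a condensed article may leave the T2 analysis to the full protocol or SAP. That stands: silence on the T2 analysis is not the fault here. The wording is, because no later document can make data from one arm show necessity.

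Second, a reader might infer that no early randomised comparison of TRAP with EMDR is planned at all. That is too strong. CRIES-13 is collected at each session in both arms, and its mixed model with time by condition permits such a comparison over the first 12 sessions. It is a self-report monitoring scale, so the gap is confined to CAPS-CA and the T2 questionnaires.

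Third, the proposed contrast has limits. Its detectable difference of 5.8 to 6.9 points exceeds the 5-point margin, it sets TRAP alone against EMDR alone, and it does not answer necessity either. All of that is right. It is offered as a supportive estimate with an interval, not as a test of non-inferiority or of need.

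Fourth, equal timing rests on an eligibility criterion about weekly attendance, and the article gives no visit windows. This also stands and calls for a check of dates.

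**Conclusion.** The point holds as a correction to what the article says T2 can show, together with a better use of data already scheduled. The T1 to T2 change in TRAP + EMDR is uncontrolled and cannot isolate an effect of TRAP. Need for TRAP before EMDR is addressed by the randomised comparison at T3 and T4. The contrast of T2 in TRAP + EMDR with T3 in EMDR-only is randomised and would estimate the CAPS-CA difference to within about 4 to 5 points. This assumes SD 10.4 in both arms, correlation 0.5, 27 to 38 analysed per arm, and sessions delivered about weekly.

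Two further inferences are not supported. The trial's main conclusion is not put at risk, since the primary non-inferiority analysis and the sample size do not depend on T2. Nor do the documents fix how large regression to the mean would be: the 2.5 to 5 points rest on an assumed selection gap, and a within-arm change should not be read against the between-arm margin.

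**What to change.** 1. In the CAPS-CA section, Measurements and the Discussion, describe the T1 to T2 change within TRAP + EMDR as descriptive. Delete the claim that T2 informs the necessity of TRAP, and refer that question to the randomised T3 and T4 comparison.
2. Prespecify, before analysis, a supportive comparison of T2 in TRAP + EMDR with T3 in EMDR-only, adjusted for T1, in the groups as randomised, for CAPS-CA, DERS, RSES and ECR-RC. State the estimand as 12 sessions of TRAP against 12 sessions of EMDR at about equal time since randomisation. Say explicitly that it is neither TRAP against no treatment nor a test of necessity.
3. Tabulate actual days from randomisation to these two visits by arm, and qualify the comparison if they differ.

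The cost is some rewording, a check of dates, and four extra supportive comparisons (five if ECR-RC mother and father are analysed separately). No new data are needed.

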### Baseline

#### The adolescent dissociative experience scale

The Adolescent Dissociative Experiences Scale (A-DES) [27] is a self-report scale used to measure the frequency of dissociative experiences among adolescents. The answers to the 30 items are marked on an 11-point scale ranging from 0 (never) to 10 (always). The total A-DES score is the mean of all item scores (range, 0–10). A mean score of 4.0 (Armstrong et al., 1997) is a commonly used cut-off for pathological dissociation. The A-DES has four theoretically derived subscales: amnesia, depersonalization/derealization, absorption, imaginative involvement, and passive influence. The A-DES has good internal consistency and test–retest stability and has proven to be valid across different cultural settings. The A-DES will be administered at T1.

#### Demographics

Demographic information of the participants will be collected from medical files and/or intake questionnaires. The gathered information will consist of age, sex, family structure, diagnoses of the child, school functioning, and socioeconomic status (SES) of the family.

### Secondary outcomes

#### The experiences in close relationships scale-revised child version

The Experiences in Close Relationships Scale-Revised Child version (ECR-RC) [28] is a self-report questionnaire on parent–child attachment that consists of 12 statements about the adolescents’ mother or father. Using a scale from 1 (not at all) to 7 (very much), six items tap into attachment anxiety (e.g., ‘I worry that my father/mother does not really love me’), and six items tap into attachment avoidance (e.g., ‘I prefer not to tell my father/mother how I feel deep down’). The reliability and validity of the ECR-R–C have been demonstrated in several independent samples. In terms of reliability, the ECR-R–C showed high levels of internal consistency, and in terms of validity, the ECR-R–C subscales correlated with depressive symptoms, emotion regulation strategies, and parenting dimensions [29, 30].

#### Difficulties in emotion regulation scale

Emotion dysregulation will be measured using the Difficulties in Emotion Regulation Scale (DERS) [31]. The DERS is a 36-item self-report questionnaire that measures six domains of emotion regulation difficulties: non-acceptance of negative emotions, difficulties in engaging in goal-directed behaviors, difficulties in accessing effective emotion regulation strategies, impulsivity, limited emotional awareness, and limited emotional clarity. The items were rated from 1 (almost never) to 5 (almost always). Higher DERS scores indicate greater emotion regulation difficulties. The DERS is a valid and reliable instrument for assessing emotional dysregulation [31, 32].

#### Rosenberg self-esteem scale

The Rosenberg Self-Esteem Scale (RSES) [33] will be used to assess self-esteem. It is a widely used 10-item Likert-type scale that measures self-esteem. Items are answered on a 4-point scale, from strongly agree to strongly disagree, measuring positive and negative feelings towards the self. The Dutch version of the RSES is a one-dimensional scale with high internal consistency and congruent validity, and a Cronbach’s alpha of 0.89 [33].

#### Revised child anxiety and depression scale

The Revised Child Anxiety and Depression Scale (RCADS) is a 47-item youth self-report questionnaire [34] with subscales including separation anxiety disorder (SAD), social phobia (SP), generalized anxiety disorder (GAD), panic disorder (PD), obsessive–compulsive disorder (OCD), and major depressive disorder (MDD). It also yields a Total Anxiety Scale (sum of the five anxiety subscales) and a Total Internalizing Scale (sum of all six subscales). Items are rated on a 4-point Likert scale ranging from 0 (“never”) to 3 (“always”). Additionally, the Revised Child Anxiety and Depression Scale – Parent Version (RCADS-P) similarly assesses parental reports of youth symptoms of anxiety and depression across the same six subscales.

